# The FOAM study: is Hysterosalpingo foam sonography (HyFoSy) a cost-effective alternative for hysterosalpingography (HSG) in assessing tubal patency in subfertile women? Study protocol for a randomized controlled trial

**DOI:** 10.1186/s12905-018-0556-6

**Published:** 2018-05-09

**Keywords:** Hysterosalpingo foam sonography (HyFoSy), Hysterosalpingography (HSG), Fertility work-up, Tubal patency testing, Ongoing pregnancy, Cost-effectiveness, Subfertility, Randomized controlled trial, Budget impact

## Abstract

**Background:**

Tubal pathology is a causative factor in 20% of subfertile couples. Traditionally, tubal testing during fertility work-up is performed by hysterosalpingography (HSG). Hysterosalpingo-foam sonography (HyFoSy) is a new technique that is thought to have comparable accuracy as HSG, while it is less expensive and more patient friendly. HyFoSy would be an acceptable alternative for HSG, provided it has similar effectiveness in terms of patient outcomes.

**Methods/design:**

We aim to compare the effectiveness and costs of management guided by HyFoSy or by HSG. Consenting women will undergo tubal testing by both HyFoSy and HSG in a randomized order during fertility work-up. The study group will consist of 1163 subfertile women between 18 and 41 years old who are scheduled for tubal patency testing during their fertility work-up. Women with anovulatory cycles not responding to ovulation induction, endometriosis, severe male subfertility or a known contrast (iodine) allergy will be excluded. We anticipate that 7 % (*N* = 82) of the participants will have discordant test results for HyFoSy and HSG. These participants will be randomly allocated to either a management strategy based on HyFoSy or a management strategy based on HSG, resulting in either a diagnostic laparoscopy with chromopertubation or a strategy that assumes tubal patency (intrauterine insemination or expectant management). The primary outcome is ongoing pregnancy leading to live birth within 12 months after randomization. Secondary outcomes are patient pain scores, time to pregnancy, clinical pregnancy, miscarriage rate, multiple pregnancy rate, preterm birth rate and number of additional treatments. Costs will be estimated by counting resource use and calculating unit prices.

**Discussion:**

This trial will compare the effectiveness and costs of HyFoSy versus HSG in assessing tubal patency in subfertile women.

**Trial registration:**

Dutch Trial Register (NTR 4746, http://www.trialregister.nl). Date of registration: 19 August 2014.

## Background

Subfertility, defined as the inability to conceive within 12 months of unprotected intercourse, affects 1 out of 6 couples trying to get pregnant [1]. Traditionally, the diagnostic work-up for subfertility includes tests to assess tubal status, among which hysterosalpingography (HSG) and diagnostic laparoscopy with chromopertubation (DLS) are the most established tests [2]. HSG is still the test of first choice during the fertility work-up in many clinics in the Netherlands. In case bilateral tubal pathology is suspected, a DLS is performed which is considered the clinical reference standard. DLS is an invasive test under general anesthesia that allows direct visualization of the pelvis, including fallopian tubes, ovaries and uterus. However, there is a risk for visceral damage, intra-abdominal bleeding and risks related to general anesthesia. Initially, hysterosalpingo-contrast sonography (HyCoSy) has been proposed as an alternative for HSG as a first line office tubaI patency test. The accuracy of HyCoSy is comparable to that of HSG [3, 4]. However, the commonly used echogenic medium for HyCoSy Microcrystalline suspension (Echovist®, Schering AG, Berlin, Germany), is no longer available. In 2011, hysterosalpingo-foam sonography (HyFoSy) was introduced as a new technique for tubal patency testing and an alternative for HyCoSy [5]. This imaging technique is comparable to HyCoSy, but it uses foam instead of gel.

The advantages of HyFoSy over HSG are manifold; with HyFoSy there is no radiation exposure which makes it a more patient friendly examination compared to HSG. In addition, the HyFoSy procedure is less painful as well as less time consuming compared with HSG [6] and a HyFoSy can be performed by the gynecologist during regular office hours, establishing the fertility work-up in a one stop clinic.

Two small observational cohort studies have been published reporting on the diagnostic performance of HyFoSy [7, 8]. An observational cohort study in 20 subfertile women found a 100% agreement between tubal patency data according to HyFoSy testing and DLS [8]. In a prospective observational cohort study in 73 women, HyFoSy was able to demonstrate two-sided tubal patency in 57 women, but technically unsuccessful in terms of inadequate filling of the uterine cavity in 6 women, while two-sided tubaI patency could not be demonstrated in 10 other women. A subsequent HSG in those 10 participants confirmed tubal occlusion in 5 (7%). In the remaining 5 women (7%) there was discordance between HyFoSy and HSG. The authors concluded that using HyFoSy as first line tubal test during the fertility work-up could avoid an HSG in about 78% of the cases (57 out of 73) [7]. There are no large studies that assess HyFoSy and HSG.

HyFoSy would be an acceptable alternative to HSG for tubal patency testing during fertility work-up in subfertile women if it leads at least to similar outcomes, in terms of live births, but lower costs. This randomized trial with a discordancy design compares two management strategies, one in which management is guided by HyFoSy and one that is guided by HSG.

## Methods / design

### Design

The FOAM study is a multicenter prospective comparative study with a randomized controlled trial design (Fig. 1) [9]. It will be performed in hospitals that collaborate within the Dutch Consortium for Studies in Women’s Health and Reproduction. Participating centers can be district, teaching or university hospitals. Gynecologists and/or ultrasound technicians will be trained in their center in the performance of the HyFoSy by one of the physicians familiar with HyFoSy (VM, KD or [name]).

**Fig. 1 Fig1:**
[figure not shown]
Flowchart FOAM study. ^1^Management based on the prognostic model of Hunault for natural conception: > 30%: 6 months expectant, followed by 6 cycles intrauterine insemination (IUI); < 30%: 6 cycles IUI, followed by in-vitro fertilization (IVF). ^2^Questionnaires: Short-Form-36 (SF-36), Health and Labour Questionnaire (HLQ)

### Participants / eligibility criteria

Subfertile women, between 18 and 41 years old, who are scheduled for tubal patency testing as part of the fertility work-up are eligible for inclusion. Women with anovulatory cycles not responding on ovulation induction, endometriosis, severe male factor (Total motile sperm count < 1 × 10^6^/ml) or a known contrast (iodine) allergy will be excluded.

### Study procedures

All consenting participants will be scheduled for both HyFoSy and HSG. The order of these tests will be determined by randomization. Both tubal patency tests will be done within the two weeks of the follicular phase of the cycle after complete cessation of menstrual bleeding. The physician performing the HSG will be blinded for the results of the previously performed HyFoSy and vice versa. Test results of HyFoSy and HSG will be classified as normal, one-sided tubal pathology or double-sided tubal pathology.

lf the results of both tubal patency tests are concordant, the planned fertility treatment will be based on the test results in accordance with the current Dutch guideline [2]. Participants with one or two patent tubes at HyFoSy and HSG will be treated according to their prognosis for natural conception based on the model of Hunault [10]. In case the chance of natural conception within the following 12 months exceeds 30%, participants will be counseled for expectant management for 6-12 months. In case the chance is less than 30%, participants will be treated with intrauterine insemination (IUI) eventually followed by in vitro fertilization (IVF). In case HyFoSy and HSG are concordant in the diagnosis of suspected bilateral tubal occlusion, participants will be scheduled for DLS, followed by IVF in case bilateral tubaI occlusion is confirmed. In case of one-sided or two-sided patency during DLS the subsequent fertility treatment will also be based on the Hunault prognosis for natural conception.

Participants in whom the results of the tubaI patency tests HyFoSy and HSG are discordant will subsequently be included in a randomized trial in which they will be randomized between management based on the results of HyFoSy or management based on the results of HSG.

Consequently, in case unilateral or bilateral patent tubes are observed by the allocated tubal patency test, subsequent management will be according to the assumption of tubal patency. This will be 6 to 12 months expectant management in case of a probability of more than 30% for a natural conception according to the model of Hunault [10], while in case of a probability of less than 30% for spontaneous conception, IUI will be recommended. If bilateral occlusion is observed by the allocated tubal patency test, subsequent management will be a DLS, and if tubal occlusion is confirmed, the next step will be IVF. In case DLS shows tubal patency of at least one tube, subsequent management will be just as in the trial arm assuming tubal patency, i.e. expectant management or IUI.

#### HSG procedure

During an HSG approximately 10 cm^3^ of water soluble or oil soluble iodinated contrast medium (depending on local protocol of the participating hospitals) will be infused in the uterine cavity and fallopian tubes through the use of a Semm cup (a plastic vacuum cup that will be placed on the cervix) or balloon catheter. The contrast medium will be visible on X-ray. During instillation of the contrast medium into the uterine cavity and fallopian tubes a series radiographs (6-8) will be made to establish the patency of the fallopian tubes.

#### HyFoSy procedure

During a HyFoSy procedure approximately 10 cm^3^ of foam will be introduced, through a little cervical balloon-less applicator, into the uterine cavity. This applicator is connected to a syringe with foam. This foam is created by rigorously mixing 5 ml ExEm-gel® (containing hydroxyethyl cellulose and glycerol, IQ Medical Ventures BV, Delft, The Netherlands) with 5 ml of purified water in a 10 ml syringe. This recipe has turned out to be excellent for creating foam that is sufficiently stable to show echogenicity for at least 5 min and for providing sufficient fluid to pass through patent tubes. [5] During infusion of the foam into the uterine cavity a transvaginal ultrasound will be made, to show whether the fallopian tubes are patent.

#### DLS procedure

Diagnostic laparoscopy will be performed under general anesthesia in a daycare setting. The technique used is a double-puncture technique. The optic will be introduced through a trocar in the belly button. A suprapubic trocar is placed to make manipulation possible. A Foley catheter is placed in the uterine cavity. During the laparoscopy methylene blue is introduced into the uterine cavity through the Foley catheter and the patency of the fallopian tubes can be confirmed under direct vision by the optic. The amount of methylene blue injected will be variable, depending on the time necessary to assess tubal function.

##### Recruitment, consent and randomization, collection of data

Eligible women receive oral and written information during their regular outpatient visit by the attending gynecologist or fertility doctor. Women will be contacted by telephone for further information by the investigator. Women who agree to participate will be asked to sign written informed consent, of which they will receive a copy at their next visit, when the informed consent form will also be signed by the investigator, supervising gynecologist, the attending registrar or fertility doctor. Women who decline randomization will be offered the standard tubal patency testing with HSG or DLS, depending on the standard management policy in the clinic. Women refusing participation are registered.

Consenting eligible women undergo a HyFoSy as well as an HSG in a random order. Randomization is stratified for each center and will be performed after baseline data have been entered in a central web-based system that is available in our research consortium (ALEA) with the use of a permuted block design. Randomization is performed with only initials and year of birth of the participants. Linking personal data to the study number can only be performed in the local participating centers. Written informed consent forms are stored in every center in a lockable room. All forms and data will be archived for 15 years in the participating centers.

When there is discordance between the results of HSG and HyFoSy participants will be randomly allocated by the web based randomization program (ALEA) for management based on either HyFoSy or HSG.

After inclusion, all measurements will be systematically recorded using an electronic Clinical Report Form. These electronic forms will be stored in a digital database. Data are handled confidentially and, whenever possible anonymously. A subject identification code list will be used to link the data to the subject, where it is necessary to be able to trace data to an individual subject. The code will not be based on the woman’s initials and birth date, the key to the code will be safeguarded by the local investigator. The handling of personal data will comply with the Dutch Personal Data Protection Act (in Dutch: De Wet Bescherming Persoonsgegevens, Wbp).

All participants will receive a questionnaire about pregnancy outcomes 12 months after randomization. Participants with discordant test results will receive digital online secured questionnaires on day 1 after randomization and after, 3, 6 and 12 months respectively. Questionnaires include information on quality of life (SF-36: Short-Form-36) [11, 12] and absence from work (HLQ: Health and Labour Questionnaire) [13].

All adverse events reported spontaneously by the subject or observed by the investigator or his staff will be recorded. All Serious Adverse Events (SAE’s) will be reported to the Medical Ethics Committee.

The recruitment of participants started in June 2015, it is expected to conclude August 2018.

##### Outcome measures

The primary outcome for the comparison of the two strategies is ongoing pregnancy leading to live birth within 12 months after inclusion. Ongoing pregnancy rate is defined as an intrauterine pregnancy with a positive heartbeat during ultrasound examination between 10 and 12 weeks of pregnancy. Secondary outcomes are pain scores (measured by Visual Analogue Scale (VAS) scores), time to pregnancy, clinical pregnancy (defined as an ultrasound visible gestational sac with or without heartbeat), miscarriage (defined as the presence of non-vitality on ultrasound or spontaneous loss off pregnancy), multiple pregnancy (defined as a pregnancy of two or more fetus), preterm birth rate (defined as a delivery before 37 weeks of pregnancy), quality of life and absence of work.

#### Statistical analysis

We will estimate and compare the proportion of women with an ongoing pregnancy leading to live birth within 12 months after inclusion for two strategies: one in which management in subfertile women undergoing tubal patency testing is guided by the results of HSG and a second strategy, in which management is guided by the results of HyFoSy. To estimate this proportion, we will have to combine the outcomes observed in the concordant group, in which management will be identical for the two strategies, and in the discordant group, in which women are randomly allocated to management based on HSG or management based on HyFoSy.

The proportion of women with an ongoing pregnancy leading to live birth for each strategy will be a weighted average of the proportions observed in two groups: the concordant group and the discordant group, where the patients in the discordant group have to be counted twice, to account for the randomization, since in half of the women in the discordant group management will be guided by the other test. Lu and Gatsonis [14] have shown that this estimate is unbiased, and have provided a closed form for the variance of this estimate. They have also shown that this paired design is more efficient than an unpaired comparison of test & management strategies, especially if the proportion of women with discordant results is low. The effectiveness of management based on HyFoSy relative to management based on HSG will be expressed as a relative risk and as an absolute difference, each with 95% confidence intervals. SPSS will be used to perform the statistical analysis.

The primary analysis will be a non-inferiority test, in which we want to exclude a decrease of 2% when relying on the HyFoSy results instead of on the HSG. No interim analysis will be performed.

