#### Sample size

We assume a 50% ongoing pregnancy rate within 12 months after tubal testing, with no difference between HSG or HyFoSy. When using a non-inferiority test at a 5% significance level, the total sample size will be guided by the fraction *f* of participants with discordant results (these will be randomized). In the randomized subgroup, the corresponding non-inferiority margin will then correspond to 2% divide by the fraction with discordant results *f* [14]. Assuming the fraction with discordant results is 7% [7], the non-inferiority margin in the discordant results will be 29%. To achieve 80% power to reject inferiority, we would then need to randomize 74 women with discordant results, and the total number to be included will be 1057 (74 divide by 7%). To account for a 10% loss to follow-up, we will include 1163 participants, resulting in 82 participants with discordant results.

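### The primary estimator is unbiased but unadjusted: with the contrast resting on about 74 women, it leaves the prognosis score unused and reports only the net of two opposite management contrasts

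*Protocol article*

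**What the plan says.** The Statistical analysis section of the protocol article estimates each strategy's proportion as a "weighted average of the proportions observed in two groups: the concordant group and the discordant group". Discordant women are counted twice to allow for the randomisation. The section relies on a cited methods paper whose authors "have shown that this estimate is unbiased, and have provided a closed form for the variance of this estimate". It names no covariate and does not divide the discordant group. It also describes "the concordant group, in which management will be identical for the two strategies". The decision rule is non-inferiority: "we want to exclude a decrease of 2% when relying on the HyFoSy results instead of on the HSG".

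On the second randomisation, the recruitment section says that discordant "participants will be randomly allocated by the web based randomization program (ALEA) for management based on either HyFoSy or HSG". Stratification by centre is described together with the randomisation of test order; no stratification factor is named for this second step.

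Study procedures makes management depend on the allocated test. Bilateral occlusion on that test leads to laparoscopy. Otherwise patency is assumed and care follows the prognostic model, for example "6 to 12 months expectant management in case of a probability of more than 30% for a natural conception".

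**The concern.** Two features of the stated estimator deserve attention because so few women carry the comparison.

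- **An available predictor is unused.** The model-based probability of natural conception is calculated in this trial to direct care. It predicts conception, which is close to the primary outcome. Leaving it out keeps residual variance that adjustment might remove.
- **Opposite contrasts are netted.** For a woman occluded on HyFoSy and patent on HSG, allocation to HyFoSy means laparoscopy and allocation to HSG means none. For the reverse pattern the two are exchanged. The pooled difference adds these contrasts, and they can offset. In a non-inferiority trial, offsetting moves the result towards the conclusion hoped for. The Discussion carries that conclusion further, to comparable management decisions and substitution of one test for the other.

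At stake are a few points of power and, more importantly, what a null result can be taken to mean.

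**Working it through.** **Inputs.** From Sample size: 50% ongoing pregnancy in both strategies; discordant fraction 7%; margin 29% among discordant women (2%/7% = 28.57%, rounded up); 80% power; 74 randomised; "When using a non-inferiority test at a 5% significance level", with sidedness not stated. The share of outcome variance explained by prognosis and direction (R²) is not given and is assumed to be 0–15%. The mix of directions is also not given. The cohort cited in Background performed HSG only in the 10 women without demonstrated two-sided patency on HyFoSy, so its 7% covers one direction only.

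**1. Reproduce the plan's figure.** With 37 per arm, SE = √(2 × 0.25/37) = 0.1162. Power = Φ(0.29/0.1162 − 1.645) = Φ(0.850) = 80.2% at one-sided 5%. So 74 reproduces, and 74/0.07 = 1057. At one-sided 2.5% the same formula gives 70.4%.

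**2. Where the contrast comes from.** Concordant women contribute the same term to both strategies and cancel. The overall difference is 0.07 × (arm difference among the discordant), with SE 0.07 × 11.62 = 0.81 percentage points. The comparison does rest on about 74 women.

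**3. Gain from adjustment.** Power = Φ(0.29/[0.1162 × √(1 − R²)] − z).

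| Assumed R² | One-sided 5% | One-sided 2.5% |
|---|---|---|
| 0 | 80.2% | 70.4% |
| 5% | 82.0% | 72.6% |
| 15% | 85.6% | 77.2% |

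With the unrounded margin of 28.57%, the one-sided 5% column becomes 79.2%, 81.0% and 84.6%. As a rough allowance for fitting two extra terms, multiply the variance by 74/72. At margin 29% and one-sided 5% the powers are then 79.3%, 81.1% and 84.7%. With R² at zero, adjustment costs about one point.

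**4. What direction alone contributes.** With share w in one direction and average rates pa and pb, the variance removed is w(1 − w)(pa − pb)²/[p(1 − p)]. At w = 0.5 and p = 0.5 this is 4% for a 20-point gap and 9% for a 30-point gap. Simulating 74 women (40,000 runs per scenario) includes the small-sample cost. The ratio of stratified to pooled variance is:
- 1.01–1.02 if both directions have the same average rate, even with exactly opposite effects of ±20 or ±40 points;
- 0.98 for 40% v 60%;
- 0.92 for 35% v 65%.

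Both estimators were unbiased in every scenario. Opposite effects alone therefore give no precision gain when split; only a difference in average rate does.

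**5. What chance imbalance does.** With w = 0.5 the between-arm difference in the share of one direction has SD √(2 × 0.25/37) = 11.6 points. A 15-point imbalance with a 30-point rate gap (assumed) shifts the discordant difference by 0.15 × 30 = 4.5 points. Overall that is 0.07 × 4.5 = 0.3 points, against a margin of 2 points and an SE of 0.81.

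**The case against.** The strongest reply is that nothing is wrong. Replacing HSG with HyFoSy changes management in both directions at once, so the net effect is the estimand, and the estimator is unbiased for it. That stands. A reader might infer that pooling the directions biases the comparison; neither the article nor the simulation supports this.

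A reader might also expect precision from test order, since "The order of these tests will be determined by randomization". Every woman has both tests, and nothing in the article makes order prognostic, so no gain can be expected. Nor should chance imbalance be read as a serious threat: it is already part of the standard error, and even the adverse case above moves the overall difference by only 0.3 points.

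Covariate adjustment is commonly left to an analysis plan, and that plan is not shown. This is why the point is an improvement and not an omission. It concerns a primary estimator that the article does fix, and it falls away if the analysis plan already contains the adjustment.

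Three practical objections stand and shape the fix. One direction may be rare, so direction-specific estimates will be imprecise. The article does not say when the prognosis is computed. Results are classified at three levels, so if normal versus one-sided counts as discordant, some women belong to neither direction.

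**Conclusion.** The point holds as a recommended improvement, not as an error. The stated primary estimator is valid for the net effect, but it is crude, rests on about 74 women and omits a prognostic variable the trial already uses. The expected gain is about 2–5 power points at one-sided 5% (2–7 at 2.5%) if R² is 5–15%, before a cost of about one point for two extra terms. It is nil if R² is near zero. These figures depend wholly on the assumed R², for which the article gives no basis.

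The case for showing direction of discordance is interpretive. A null net result is compatible with equal guidance and with offsetting errors, and the net depends on a mix of directions that the planning data cannot supply.

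**What to change.** Before outcomes are analysed, specify the following:

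1. In the discordant group, estimate the arm difference from a logistic model with arm, predicted probability of natural conception (continuous) and direction of discordance, standardised to the whole discordant group, with a robust or bootstrap interval. Standardisation keeps the estimand an absolute difference between strategies.
2. Derive the prognosis from baseline data in the same way in both arms, whatever the allocation. Define direction by which test shows bilateral occlusion, and say how any discordant woman who fits neither direction is handled.
3. Combine the result with the concordant group as already planned, and keep the crude weighted average as a sensitivity analysis.
4. Report the two direction-specific differences with intervals beside the overall one, labelled descriptive.

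Do not add test order as a precision covariate. Leave the second randomisation as it is: recruitment was expected to end in August 2018, and restratifying would mean altering the live randomisation system for few women.

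The cost is wording and analysis code, plus a check that the inputs to the prognostic model are recorded for every discordant woman.
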